## Abstract

**Background:**

Over the past decade, the adoption of screening programs, digital mammography, and magnetic resonance imaging (MRI) has increased early-stage breast cancer diagnosis rates. Mortality rates have decreased due to early detection and improved treatments, including personalized therapies. Accelerated partial-breast irradiation (APBI) is emerging as a convenient and effective treatment for some patients, with studies exploring its preoperative use. Preoperative APBI, especially with MRI guidance, offers improved tumor targeting and potentially reduced side effects. Magnetic Resonance Imaging-Guided Single-Fraction Pre-Operative Radiotherapy for Early-Stage Breast Cancer (RICE trial) aims to assess the feasibility and efficacy of MRI-guided single-dose radiotherapy (RT) for early-stage breast cancer.

**Methods:**

The RICE study is a prospective, single-arm study evaluating single-fraction preoperative, APBI treatment for patients with early-stage breast cancer using a magnetic resonance imaging linear accelerator (MRI linac). Eligible patients enrolled in this study will have a core biopsy to confirm estrogen receptor-positive and HER2-negative sub-type. RT planning will use a planning computed tomography (CT) co-registered with a MRI with the patient in either the supine or prone position. For the diagnostic workup, [18F] fluorodeoxyglucose positron emission tomography/CT ([18F] FDG PET/CT) and [18F] fluoroestradiol positron emission tomography/CT ([18F] FES PET/CT) will be performed prior to treatment. Thirty patients will receive a single ablative RT dose of 21 Gray to the tumor. Pre-treatment and post-treatment MRI scans will be acquired at baseline and 5 weeks post-RT respectively. Breast-conserving surgery will be scheduled for 6 weeks after APBI treatment using the MRI linac.

The primary study endpoint is the successful administration of a single fraction of preoperative breast RT under the guidance of an MRI linac. Secondary endpoints include evaluating the utility of MRI, [18F] FDG PET/CT, and [18F] FES PET/CT as a non-invasive method for assessing treatment response in patients undergoing single-fraction preoperative APBI.

**Conclusion:**

The RICE trial represents a significant step in breast cancer treatment, offering insights that could lead to treatment protocols with minimized RT appointments and enhanced patient outcomes.

**Trial registration:**

This trial is registered with the Australian New Zealand Clinical Trials Registry (ANZCTR). Registered 31st of May 2021. Registration number: ACTRN12621000659808.

## Background

Over the past decade, the implementation of screening programs and the adoption of digital mammography and magnetic resonance imaging (MRI) have led to an increased incidence of early-stage breast cancer diagnosis. This trend is expected to continue, driven by the increasing prevalence of risk factors, population growth, and aging [1, 2]. Despite this, mortality from early-stage breast cancer has significantly decreased, with the global 5-year net survival rate estimated to increase from 67.9 to 78.2% [3, 4]. Simultaneously, there is a shift towards personalized and less invasive therapies, aimed at de-escalating therapy, improving cosmetic outcomes, and reducing radiotherapy (RT)-related toxicity, all while ensuring the safety and efficacy of oncological care [4–8].

Currently, patients diagnosed with early-stage breast cancer typically undergo wide local excision, followed by daily postoperative whole-breast irradiation lasting anywhere from 3 to 5 weeks [9–13]. While this regimen effectively reduces tumor recurrence and decreases breast cancer mortality, the conventional post-operative treatment schedule of 3–5 weeks is prohibitively long for many patients, particularly among the elderly, rural residents, and those living in underserved regions [14, 15]. In an effort to provide greater convenience and improve the quality of life for patients and also considering that up to 90% of recurrences are found close to the lumpectomy site, hypo fractionated accelerated partial-breast irradiation (APBI) is currently being explored. APBI, a technique in which RT is delivered solely to the high-risk tissue, has emerged as a promising alternative to whole-breast irradiation [11, 16, 17]. Several phase III trials using different APBI techniques have demonstrated that, for selected patients, APBI achieves satisfactory local control comparable to that of whole-breast irradiation, but with fewer side effects, greater convenience, better quality of life, and reduced costs [7, 18, 19, 20, 21, 22, 23]. As such, APBI has recently become a standard treatment for low-risk patients [4, 7, 19, 20]. In general, patients are eligible when they meet the suitability criteria established by The European Society for Radiotherapy (ESTRO) or the American Society for Radiation Oncology (ASTRO) [4, 18, 22].

Ensuring the accurate delivery of APBI is critical, as it targets only the high-risk tumor tissue and not the entire breast. However, postoperative APBI presents challenges due to difficulties in precisely delineating the tumor from the surrounding healthy tissue, which can be affected by breast distortion and the presence of postoperative seroma [4]. Consequently, this often leads to less precise target volume definition and greater variability in delineation among Radiation Oncologists, resulting in unnecessarily large irradiated volumes [20, 24, 25].

In an effort to reduce the irradiated volume and improve cosmetic outcomes, studies are now investigating the potential use of APBI in the preoperative setting [5, 23, 25–30]. One promising alternative is preoperative magnetic resonance-guided radiotherapy (MRgRT). With the exceptional soft tissue contrast provided by MRI, delivering preoperative APBI using a magnetic resonance-integrated linear accelerator (MRI linac) allows for greater distinction between the tumor and surrounding healthy tissue, as the tumor remains in its original location [4, 6, 28, 31]. This approach leads to reduced inter-observer variability in contouring the tumor and thus enhanced definition of the tumor volume [4, 6, 28]. Furthermore, since a smaller volume of tissue is treated, preoperative APBI enables the delivery of a higher dose per fraction. This facilitates the possibility of single-dose RT treatment, further reducing the treatment burden and RT-induced toxicity to the patient, thereby significantly improving the patient's quality of life [4–8].

Another advantage of preoperative RT is the ability to noninvasively assess treatment response via imaging. Currently, in the setting of preoperative systemic therapy, treatment response assessment is performed using MRI [4, 32, 33]. However, data on treatment response assessment with MRI after preoperative RT are limited. Notably, two separate studies reported that MRI has a positive predictive value (PPV) ranging from 67 to 88% and a negative predictive value (NPV) ranging from 76 to 85% in predicting pathological complete response [4, 27, 28]. Although these studies were significantly underpowered, and more data are needed to establish the value of MRI in developing a prediction model for pathologic response, if a pathologic complete response can be more accurately predicted after preoperative APBI in the future, surgery could potentially be omitted in these low-risk patients. For patients without a pathologic complete response, single-fraction RT could replace post-operative RT schedules, and tumor downstaging leading to less healthy breast tissue being excised and improve the overall cosmetic outcome.

In the single-institution prospective study in Melbourne, Australia, which we call the Magnetic Resonance Imaging-Guided Single-Fraction Pre-Operative Radiotherapy for Early-Stage Breast Cancer (RICE) trial, our goal is to assess the feasibility of MRI-guided single-dose preoperative APBI using an MRI linac as a definitive treatment for early-stage breast cancer. We also aim to investigate the utility of MRI as a non-invasive tool for assessing treatment response after single-fraction neoadjuvant RT.

## Methods/design

### Study design

This single-arm prospective trial will be conducted at the Radiation Oncology Department of Austin Health, Melbourne, Australia.

### Primary and secondary endpoints

The primary endpoint of the study is to assess the feasibility of administrating a single fraction of preoperative RT under the guidance of an MRI linac. Feasibility is defined as achieving at least 90% participation among eligible and consenting participants who receive the full prescribed radiation dose under MRI linac guidance.

The secondary objective is to evaluate the relationship between pre-RT MRI and post-RT MRI with respect to histopathological findings.

### Patient recruitment and selection

Prospective participants for the study will be identified through two main channels: multidisciplinary meetings and direct referrals from external specialists to the Radiation Oncology Department.

Table 1 presents an overview of the inclusion and exclusion criteria, which align with the guidelines for APBI set forth by ASTRO and ESTRO [18, 34].

**Table 1 Tab1:** Overview of the inclusion and exclusion criteria for the RICE trial

Inclusion	Exclusion
Age ≥ 60 years	Previous radiotherapy to the same breast
Unifocal	Suspicious diffuse microcalcifications
Tumor visible on pre-treatment imaging	Invasive lobular carcinoma on core biopsy
Tumor size on pre-treatment imaging ≤ 2 cm	Lymphovascular invasion on core biopsy
Grade 1–2 on pre-treatment core biopsy	Any clinical nodal or metastatic disease
Estrogen receptor (ER) and progesterone (PR) positive (> 10%)	Human epidermal growth factor receptor 2 (HER2) positive
Clinically node-negative	Prior non-hormonal therapy
Breast primary tumor visible on MR radiation oncology imaging (with or without IV contrast) for treatment localization	Skin or chest wall involvement
	Collagen vascular disease (e.g., lupus, scleroderma)
	Pregnant or lactating
	Absolute contraindications to MRI (e.g., incompatible implants, unable to tolerate duration)

### Informed consent

If a subject is considered eligible based on this preliminary screening, the surgeon will provide detailed information about the clinical study. Patients interested will receive additional information from the Radiation Oncology trial coordinator. Furthermore, patients will be referred to the Radiation Oncologist at the Olivia Newton-John Cancer Center for preoperative consultation and receive further information about the RT treatment.

### Procedure

An overview of the study procedures for the trial is illustrated in Fig. 1.

**Fig. 1 Fig1:**
[figure not shown]
Overview of the study procedures for the trial

Upon entering the trial, patients will first undergo a clinical examination and core biopsy. This will be followed by treatment planning, which will involve MRI and CT simulation. For the purpose of RT planning and diagnostic workup, [18F] FDG PET/CT and [18F] FES PET/CT images of both breasts will be acquired.

Six weeks after receiving RT treatment, patients will undergo wide local excision along with sentinel lymph node biopsy.

### Pre-treatment surveillance imaging

The baseline assessment of treatment response will be conducted on an MRI simulator system (Phillips Ingenia Ambition 1.5 T MRI) utilizing the department’s 1.5 T system. The MRI is equipped with a dStream 7 Channel dedicated breast coil from Phillips Healthcare (Best, Netherlands). For this assessment, patients will assume a prone position.

### MRI linac and RT for breast sites

The Elekta Unity MR-linac (Elekta, Stockholm, Sweden) is a combination of a modified Philips Ingenia 1.5 T MRI with a split-coil superconducting magnet and a linear accelerator. The beam generation system produces a single 7-megavoltage flattening filter-free X-ray source and is mounted on an annular gantry that freely rotates around a cylindrical cryostat containing the static-field MR coils. The Unity radiation field is shaped by a multi-leaf collimator, ranging from 0.8 cm × 0.5 cm to 57.4 cm × 22.0 cm at the isocenter. The patient positioning system is capable of only longitudinal movement, making it impossible to move the treatment couch laterally or vertically. The isocenter is 14.0 cm above the patient positioning system and 143.5 cm from the source.

The challenges particularly associated with breast treatment on the MR-linac include geometric accuracy due to gradient non-linearities combined with lateral target volumes, the electron return effect, and the electron stream effect. These issues have been described and addressed by earlier studies [35], and procedures are included in the protocol for this study to minimize their impact on treatment for RICE patients. These procedures include the use of distortion correction software for geometric accuracy, carefully chosen beam angles, and organs at risk margins to minimize the effects of electron stream effect, as well as the use of bolus material to shield any predicted electron stream effect from treatment planning simulation. Strategies for online plan adaptation compensate for the fixed couch position, and online motion monitoring allows for gating (beam pause) when the target moves out of the planned high-dose volume.

### RT planning

In this study, RT planning will involve both MRI and CT simulation, conducted with the patient in either the supine or prone position. MRI simulation will occur prior to CT to ensure that the lesion is visible on the imaging sequences that are available on the integrated MRI linac, to support treatment verification and delivery. It will also be used to determine whether the patient would benefit from treatment in the supine or prone position without additional exposure to ionizing radiation. The gross tumor volume (GTV) will be contoured as the visible tumor on the CT and MRI scans. The clinical target volume (CTV) will be defined by uniformly expanding the GTV by 15 mm. This expansion will be limited posteriorly by the pectoralis muscles and an anterolateral margin of 5 mm from the skin. The volume will not extend across the midline. The PTV will be created from a 3-mm margin expansion of the CTV, to account for minor inter and intra-fraction variations in patient positioning.

Treatment planning will be completed using Monaco Treatment Planning System (Elekta Stockholm, Sweden) using step-and-shoot Intensity Modulated Radiation Therapy, with multiple beams positioned at angles optimized for target coverage and organ at risk sparing within the current MRI linac capabilities.

For the dose prescription, the plan is to ensure that 95% of the CTV receives the full prescribed single dose of 21 Gy. Additionally, 95% of the PTV is intended to receive at least 95% of the prescribed dose, while a maximum of 2% of the PTV is intended to be exposed to 107% of the prescribed dose. The dose criteria for this study were determined based on conservative consideration of available literature for similar dose prescriptions for this clinical indication [6, 29, 30].

### RT delivery

Following planning, a single 21 Gray (Gy) fraction will be delivered within 10 days of the simulation. Treatment will be administered via an MRI linac (Elekta Unity Sweden). The patient will be positioned according to the RT planning position, and a verification image will be acquired. The image will be assessed, anatomical contours adjusted, and the treatment plan adapted to match the patient’s anatomy. Treatment will be delivered with real-time cine MRI monitoring to ensure safe and accurate delivery of the dose to the PTV.

### Post-treatment surveillance imaging

Post-treatment assessment of the response will be conducted 5 weeks after treatment using the MRI simulator. The same patient positioning and protocol as established in the pre-treatment surveillance imaging step will be used; this consistency will ensure comparability between the pre-treatment and post-treatment images, allowing for accurate evaluation of the effectiveness of treatment.

### Breast-conserving surgery

Six weeks after completing RT treatment, the patients will undergo breast conservation surgery, which consists of wide local excision for removing the tumor, along with sentinel lymph node biopsy to assess for the potential spread of cancer to the lymph nodes. In cases where the sentinel lymph node is found to be positive, indicating potential cancer spread, patients will be counseled regarding the possibility of axillary clearance. The decision for this additional procedure will be made based on the discretion of the treating surgeon, considering the individual patient's condition and treatment needs.

Histopathological assessment of the excised tissue will be performed by a pathologist with a sub-specialization in breast cancer. Tumor cells will be evaluated using hematoxylin and eosin staining and cytokeratin antibody activity. The response to treatment will be graded using the Miller and Payne Reporting Criteria [36].

Tumor samples will be securely stored within the Pathology Health biobank, and blood samples will be stored in the pathology freezer.

### Follow-up

Several clinical assessments, cosmetic photographs, and formal acute toxicity scoring will be conducted by the treating Radiation Oncologist at key time points throughout the study. A baseline assessment will be performed prior to the commencement of treatment; then, follow-up assessments will be performed at 2 weeks, 6 months, and 12 months post-treatment.

The acute toxicity and cosmetic outcome scores will adhere to the standards set by the Common Terminology Criteria for Adverse Events (CTCAE) Version 5.0 [37].

All adverse events resulting from RT experienced by the participants will be documented in the case report form. Importantly, adverse events that could be influenced by the study interventions will be considered outcomes of the study.

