### Statistical methods

Descriptive summary statistics will be determined to summarize the patient clinical characteristics, responses to patient-reported outcome questionnaires, and rates of adverse events at each follow-up time point. The primary outcome will be reported as the proportion of patients who can be feasibly treated with MRI linac using a single-fraction APBI technique. The denominator includes all patients who met the study eligibility criteria and provided consent to participate. Success for this outcome will be defined as achieving this treatment outcome in at least 90% of patients. For the secondary outcome assessment, univariate analysis will be performed to investigate the association between MRI parameters and the tumor response rate. Categorical variables (i.e., Clavien–Dindo grade) will be presented as counts and percentage frequencies, while continuous variables (i.e., quality of life or patient-reported outcome measures) will be presented as the mean ± standard deviation if they are normally distributed or the median (interquartile range) if their distribution is skewed.

Pearson or Spearman’s rank correlation coefficients will be used to assess correlations for normally and non-normally distributed continuous variables, respectively. Appropriate parametric or nonparametric tests will be applied to assess associations between the MRI data and histopathological features of the patients. Additionally, the MRI results will be compared between good responders to treatment and poor responders to treatment. Receiver operating characteristic (ROC) curve analysis may be employed to determine cut-off points for evaluating associations between continuous variables and binary outcomes, such as the tumor response rate.

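### The stated rule for recording adverse events covers those resulting from RT, which is narrower than the outcome class it should feed, so events put down to surgery may not be captured

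*Protocol article*

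**What the plan says.** Two adjacent sentences in the protocol article, Follow-up, set the scope of adverse event data. The recording rule is "All adverse events resulting from RT experienced by the participants will be documented in the case report form". The outcome rule is that "adverse events that could be influenced by the study interventions will be considered outcomes of the study".

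The same section describes a second source of toxicity data: "formal acute toxicity scoring will be conducted by the treating Radiation Oncologist at key time points throughout the study". The grading standard is CTCAE version 5.0. After a baseline assessment, "follow-up assessments will be performed at 2 weeks, 6 months, and 12 months post-treatment".

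Two features of the design bear on this. Study design says "This single-arm prospective trial will be conducted at the Radiation Oncology Department", so there is no comparator. Breast-conserving surgery says "Six weeks after completing RT treatment, the patients will undergo breast conservation surgery", so the 6- and 12-month assessments come after both RT and surgery.

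Statistical methods plans descriptive summaries that include "rates of adverse events at each follow-up time point". It also gives Clavien–Dindo grade as its example of a categorical variable to be tabulated.

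**The concern.** The recording rule makes a causal judgement a condition of entry. The outcome rule asks only whether the study interventions could have influenced the event. Events that meet the second test but not the first are outcomes with no stated route into the case report form.

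Here that group is not marginal. A wound problem, infection or seroma in a breast irradiated six weeks before excision may come from RT, from surgery or from both. How RT before surgery affects the surgical course is a natural safety question for this sequence, and these are the events on which the two sentences part. The stated toxicity assessor is the treating Radiation Oncologist, who knows that every patient was irradiated, and no control arm would expose an attribution error.

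An analysis plan cannot repair this later, because analysis cannot recover events that were not entered. Reduced RT toxicity is part of the rationale given in the Background, so the safety summary will be read with interest even though it is descriptive.

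**Working it through.** **1. The scope of each sentence.**

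- Recording rule: events resulting from RT. The test is causation and the exposure is RT.
- Outcome rule: events that could be influenced by the study interventions. The test is possible influence, and the exposure is worded more broadly.
- Clavien–Dindo grade in Statistical methods: implies that surgical complications are to be tabulated. The recording rule in Follow-up does not provide for them.

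Even if the study interventions were RT alone, the outcome class would remain the wider one, because possible influence is a weaker test than causation.

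**2. Whether the scheduled scoring closes the gap.** Visit times are read as counted from RT. The post-treatment imaging section uses the word treatment in that sense, with a scan at 5 weeks and surgery at 6.

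- Toxicity visits after baseline: week 2, 6 months (about week 26) and 12 months.
- Surgery: week 6.
- Interval from surgery to the next listed toxicity visit: 26 − 6 = about 20 weeks.

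The contact 2 weeks after surgery in Patient-reported outcomes is for questionnaires, not clinician toxicity scoring. A complication that starts and resolves within these 20 weeks would therefore depend on the event log, and the stated rule for that log turns on cause.

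**3. The effect of attribution on the recorded rate.** The documents give no toxicity rate and no attribution accuracy, so the inputs are assumptions, shown as ranges:

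- share of patients with an RT-caused event, pR: 10% to 30%
- share with an other-cause event, pO: 10% to 30%, independent of the first
- share of RT-caused events attributed to RT, s: 60% to 100%
- share of other-cause events attributed to RT, f: 0% to 30%

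If the log holds only events attributed to RT:

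- all-cause rate = 1 − (1 − pR)(1 − pO)
- recorded rate = 1 − (1 − pR·s)(1 − pO·f)

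Since s and f are at most 1, the recorded rate cannot exceed the all-cause rate. With pR = 20% and pO = 30%, the all-cause rate is 1 − 0.80 × 0.70 = 44%. The recorded rates are:

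| s | f | Recorded rate | Against RT-caused 20% | Against all-cause 44% |
|---|---|---|---|---|
| 1.0 | 0 | 1 − 0.80 × 1.00 = 20.0% | 0 | −24.0 points |
| 0.6 | 0 | 1 − 0.88 × 1.00 = 12.0% | −8.0 points | −32.0 points |
| 0.8 | 0.3 | 1 − 0.84 × 0.91 = 23.6% | +3.6 points | −20.4 points |
| 1.0 | 0.3 | 1 − 0.80 × 0.91 = 27.2% | +7.2 points | −16.8 points |

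Over the whole grid, the recorded rate is 5 to 33 points below the all-cause rate. Against the RT-caused rate the error runs from about −12 to +8 points.

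**4. The plan's own figure.** The only precision stated is for feasibility: a Wilson 95% interval of 74.4% to 96.5% at 90% of 30 patients. For 27/30 this reproduces as 74.38% to 96.54%. It does not depend on adverse event recording.

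**The case against.** The strongest reply is that the rule promises to record RT-related events and does not say that others are left out. That stands. A reader might infer that events put down to surgery are never written down, but the documents do not say so. The scheduled CTCAE scoring has a baseline and is not made conditional on cause. The mention of Clavien–Dindo grade suggests that surgical complications are expected in the data. Photographs and quality-of-life questionnaires add further records that do not depend on attribution.

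A reader might also infer that reported RT toxicity must be biased downward. That is not supported either. The shortfall is certain only against the all-cause rate, and only if the log holds nothing but RT-attributed events. Against the RT-caused rate, a treating Radiation Oncologist may credit a surgical event to RT as well as the reverse, and some post-surgical events are correctly put down to surgery.

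Finally, an article condenses its protocol, and details of event summaries belong in an analysis plan. That disposes of any complaint about how rates are tabulated. It does not remove the mismatch between two adjacent sentences, both stated, on what is recorded and what counts as an outcome.

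**Conclusion.** The point holds as a mismatch of scope that is cheap to correct. As written, the recording rule does not cover every event that the next sentence counts as an outcome, and it does not provide for the surgical complications implied by the analysis section. The events most exposed are those put down to surgery that resolve in the roughly 20 weeks before the 6-month visit; these may not be captured.

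A rate built on the rule depends on the assessor's attribution. It understates the all-cause rate and can err either way against the RT-caused rate. The sizes given rest wholly on assumed event rates and attribution shares, on independence of the two kinds of event, and on a strict reading of the rule. The 20-week gap rests on visits being counted from RT.

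The consequence is limited. Toxicity is neither the primary endpoint nor the stated secondary objective, and it carries no test or threshold. The feasibility result and the sample size do not change.

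**What to change.** In Follow-up, replace the recording sentence with a rule that all adverse events from the RT fraction to the 12-month visit are documented regardless of cause. Each event should carry its CTCAE grade and a separate attribution field (RT, surgery, both, neither). The recorded set then contains the outcome class, and attribution can be reviewed afterwards. Report the all-cause and the RT-attributed rates.

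The cost is a change of protocol and case report form wording, one extra field and slightly more data entry. Reported event rates will look higher, because events put down to surgery will be included. No visit, treatment or sample size changes.
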